### Statistical Analysis

#### Overview

All randomized individuals will be included in analyses, following intention-to-treat principles. Missing data will initially be handled by available case analysis under the missing completely at random (MCAR) assumption. Systematically missing data will invalidate the MCAR assumption; thus, evidence of such will be sought. If data are missing systematically, then it may be the case that early responders differ from nonresponders and, in extension, that late responders are more like nonresponders. Therefore, one analysis will regress primary outcomes against the number of attempts to collect follow-up data before a response was recorded. Attrition analyses will further explore the MCAR assumption by investigating if responders and nonresponders are different with respect to baseline characteristics.

We anticipate approximately a 10%-20% attrition rate, as this is what we have experienced in previous trials of text messaging interventions in Sweden when we used a similar scheme for data collection [11,14,26-28]. We have no reason to believe that attrition rates will be different between recruitment settings, as all follow-up procedures will be the same, but we will investigate such differences and report our findings in light of them. Sensitivity analyses that include imputed values for missing outcome data will be performed, and limitations of the imputed analyses will be considered in face of the actual attrition rate. In addition, data will be graphically examined for outliers or data input errors, and sensitivity analyses will be performed excluding any erroneous data points.

We will estimate all models using Bayesian inference [29-31] and report the marginal posterior probability of an effect of group allocation on each of the outcomes. We will use the median as a point estimate of the effect and report 95% compatibility intervals. We will complement the Bayesian inference with null hypothesis tests at the .05 significance level. Both posterior distributions and significance tests will create a basis for scientific inference.

#### Models

Baseline characteristics will be compared between the intervention and control groups using Fisher exact tests and Mann-Whitney U tests. Using logistic regression, we will compare characteristics of participants recruited through the online setting versus those through facilitated recruitment and between those eligible for the general version versus the surgery version of the intervention.

For the primary and secondary outcome measures, differences between the 2 groups (control and intervention) at the different follow-up stages with respect to prolonged abstinence, point prevalence of smoking abstinence, and 7-day point prevalence will be analyzed using logistic regression. Negative binomial regression will be used to analyze the number of quit attempts, use of other smoking cessation services, and cigarettes smoked weekly (among those who still smoke). Models will be adjusted for baseline characteristics (gender, age, nicotine dependence, importance, self-efficacy, and know-how) as well as the stratifying variable in the randomization procedure (general or surgery eligibility).

Effect-modification analyses will be performed for the 2 primary outcomes. The following potential effect modifiers measured at baseline will be explored: gender, age, years of smoking, mean number of cigarettes smoked weekly, use of snus, nicotine dependence, importance, self-efficacy, and know-how. In addition, effect modification based on which setting (online or primary health care) participants were recruited will be explored and which version of the intervention they were eligible for (general vs surgery). Effect-modification analyses will be performed by including interaction terms in the adjusted regression models for each potential moderator (one model per moderator).

For the mediator outcomes, mediators will be explored using a causal inference framework [32-34] using Bayesian inference to estimate the natural direct effect and natural indirect effect (as per the definitions of Pearl [34]). We will report on the posterior distributions of these 2 estimates, as well as the proportion of the total effect that is accounted for by the natural indirect effect. Four models will be created for each primary outcome measure, 3 investigating the mediating factors on their own and a fourth incorporating all mediators at once. If any baseline characteristics are found to moderate the effect in the primary analysis, then additional mediator models will be created to include these as moderators.

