### Trial Design

A 2-arm, parallel-group (1:1) RCT will be employed to address the study objectives. The trial will follow a Bayesian group sequential design [19-21] (see Sample Size). All participants will receive treatment as usual; however, participants who are allocated to the intervention arm will also be given access to a text message smoking cessation intervention.

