#### Interventions

Both the intervention and control groups will be given treatment as usual, and neither will be restricted from using other available smoking cessation aids. The intervention group will in addition be given access to a text message intervention.

Treatment as usual will in this trial be defined as follows. For participants recruited through online advertisements, it is defined as referral to national quit lines (sluta-röka-linjen [22]) and general information about smoking and health (1177 Vårdguiden [23]). For participants recruited through primary health care units, it is defined as referral to national quit lines (sluta-röka-linjen [22]) and referral to general information about smoking and health (1177 Vårdguiden [23]). In addition, primary health care units will offer all smokers a meeting with a nurse or smoking cessation specialist to have a conversation about smoking cessation and health.

Participants allocated to the intervention group will be given access to a text message intervention. Two versions of the intervention exist: one general version and one that has been tailored specifically for individuals undergoing elective surgery. Both versions are based on findings from our previous research [11-18]. The elective surgery intervention will be allocated to participants in the intervention group who report having elective surgery planned in the next 3 months.

Both versions of the intervention consist of a 12-week text message program with messages sent to participants’ mobile phones on a daily basis. Over the first few weeks, all participants will receive 2-4 messages per day, which will be reduced to 2 messages per day during the middle part of the intervention and further reduced to 1 message per day during the latter part of the intervention. The content of the messages is primarily informational and encouraging, and some messages ask participants to do certain tasks, such as throw away ashtrays. None of the messages ask participants to respond, but participants can request extra supportive messages by sending a text message with 1 of 3 keywords: weight, relapse, or craving. A message is then sent back to participants with specific information about potential weight gain, what to do if one relapses and has a cigarette, or help if they are experiencing nicotine cravings.

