### Assignment of Interventions

Allocation will be done according to a computer-generated random sequence. Prior to randomization, participants will be stratified according to which of the 2 versions of the intervention is appropriate (general or surgery). Block randomization will be used to ensure equal number of participants in each group within stratum. Random block sizes of 2 and 4 will be used in order to prevent subversion of allocation concealment.

Randomization will be done immediately after responding to the baseline questionnaire, which is done by participants on their mobile phones. Once responses are received by the backend server, automatic randomization will take place, and participants will be told about group allocation via a text message. Research personnel will not be able to affect the allocation.

Participants will be aware of their group allocation; however, research personnel will be blinded. All questionnaires are completed by participants on their own mobile phones, without supervision by research personnel. These automated procedures ensure no unblinding. Nonresponders to questionnaires will be called by phone (see Data Collection), and during this time, it is possible that participants will reveal their allocation to assessors (see Generalization and Limitations).

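### Follow-up weekly cigarettes is modelled without its own baseline value, and recruitment setting is left out of the main covariate list; both are already collected

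*Protocol article*

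**What the plan says.** The Models section of the protocol assigns logistic regression to the abstinence outcomes. It assigns negative binomial regression to quit attempts, use of other cessation services, and weekly cigarettes among those still smoking. One adjustment rule then covers all of these models: "Models will be adjusted for baseline characteristics (gender, age, nicotine dependence, importance, self-efficacy, and know-how) as well as the stratifying variable in the randomization procedure".

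The next paragraph lists the baseline moderators to be explored. They include "years of smoking, mean number of cigarettes smoked weekly, use of snus, nicotine dependence, importance, self-efficacy, and know-how". It adds that "effect modification based on which setting (online or primary health care) participants were recruited will be explored". Each moderator is handled by "including interaction terms in the adjusted regression models for each potential moderator (one model per moderator"). Both variables are therefore available for analysis, but only as moderators of the two primary outcomes.

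Two other sections bear on setting. Under Interventions, usual care in both settings includes referral to the quit line and to general information, and in addition "primary health care units will offer all smokers a meeting with a nurse or smoking cessation specialist". Under Assignment of Interventions, "participants will be stratified according to which of the 2 versions of the intervention is appropriate (general or surgery"), so setting is not a stratum.

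**The concern.** For an outcome that is also measured at baseline, the baseline value is usually the strongest single predictor of follow-up. Here it is collected and then left out of the one model where it matters most, so the interval for that outcome is wider than it needs to be. There is a second reason to include it. The weekly-cigarettes analysis is restricted to people who still smoke, which is a condition that arises after randomization. Randomization therefore no longer guarantees that baseline consumption is balanced in the analysed subset.

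For setting, the protocol itself gives reasons to expect different outcomes. Usual care differs, and Generalizability and Limitations describes online recruits as actively seeking help and primary care recruits as less likely to be. With no stratification by setting, the arms can differ by chance in their mix. A main effect for setting would absorb that.

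**Working it through.** The protocol gives no sample size, control rate or power, so there is no planned figure to reproduce. Every strength of association below is an assumption. From the documents come the covariate list, 1:1 allocation, the OR of 1.36 from a cited meta-analysis (used only as an illustrative effect), the .05 level, and the OR 1.3 target.

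**1. Weekly cigarettes (log-scale approximation).** Let r_yb be the correlation of follow-up with baseline cigarettes, and r_bd that of baseline cigarettes with nicotine dependence, which is already in the model. If dependence predicts follow-up only through baseline consumption, r_yd = r_yb × r_bd. The residual variance after adding baseline, relative to before, is

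(1 − r_yb²) / (1 − r_yd²).

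Both correlations are assumed to lie between 0.5 and 0.7.

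| r_yb | r_bd | r_yd | Variance ratio | Variance cut | SE cut |
|---|---|---|---|---|---|
| 0.5 | 0.7 | 0.35 | 0.75/0.8775 = 0.855 | 14.5% | 7.5% |
| 0.6 | 0.6 | 0.36 | 0.64/0.8704 = 0.735 | 26% | 14% |
| 0.7 | 0.5 | 0.35 | 0.51/0.8775 = 0.581 | 42% | 24% |

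A separate simulation used negative binomial fits directly. It assumed 600 continuing smokers, slope 0.8 on log baseline, dispersion 0.3, and correlation 0.6 with dependence. The mean SE of the log rate ratio was 0.0550 without and 0.0463 with baseline. The variance ratio is (0.0463/0.0550)² = 0.71, or 29% less variance, which lies inside the range above.

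**2. Primary logistic outcomes.** Large-sample logistic fits were compared with and without setting and baseline cigarettes, with dependence and one further prognostic covariate already in the model. Assumptions: control abstinence 10 to 30%; setting OR 1.5 to 2.0; 30 to 50% recruited from primary care; cigarettes OR 1.0 to 0.7 per SD given dependence; correlation of cigarettes with dependence 0.6; conditional treatment OR 1.36.

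- The SE of the log OR rises by 0.2 to 2.1% when the two covariates are added.
- The OR moves from 1.343–1.358 up to 1.36.
- The ratio of squared Z is 1.004 to 1.041, equivalent to about 0.4 to 4% more participants. Setting alone gives 1.004 to 1.026.
- Power rises by about 0.1 to 1.7 points at a total of 1000 or 2000 participants.

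**3. Chance imbalance in setting.** With n participants and primary care share p, the SD of the between-arm difference in share is √(2p(1−p)/(n/2)). For p = 0.3 to 0.5 this is 0.20 to 0.22 at n = 20 and 0.09 to 0.10 at n = 100. Multiplied by ln 1.5 to ln 2.0 (0.41 to 0.69), a one-SD imbalance shifts the log OR by about 0.08 to 0.16 at n = 20 and 0.04 to 0.07 at n = 100. The target is log(1.3) = 0.26. For comparison, if abstinence were 20%, the SE of the unadjusted log OR at n = 100 would be about √(2/(50 × 0.16)) = 0.50. The imbalance is thus a small part of the total uncertainty.

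**The case against.** The strongest reply is that the primary analysis is sound as written. The list is prespecified and includes the stratifying variable and the main psychosocial predictors. Importance, self-efficacy and know-how may already carry much of the motivational difference between settings. Nothing in the protocol shows that setting or cigarettes predicts abstinence once those are in the model. Setting is also examined elsewhere: as a moderator, in a comparison of controls, and in the attrition checks. For the primary outcomes this reply largely stands.

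Three stronger readings are tempting, and the documents do not support them.

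- A reader might infer that the primary models lose precision. In logistic regression the SE is slightly smaller without the covariates; the cost is mild attenuation of the OR.
- A reader might infer that the OR 1.3 target becomes materially harder to reach. Shrinking a conditional OR of 1.30 to 1.25 requires omitted variation with an SD of 1.0 on the logit scale. Setting with OR 2.0 and an even split has SD 0.5 × ln 2 = 0.35; adding cigarettes at OR 0.7 per SD brings the total to about 0.45 to 0.50. At 0.5 the OR falls only to 1.29. The Sample Size section also treats the criteria as targets, not binding rules.
- A reader might infer that pooling two usual-care backgrounds confounds the comparison. Allocation is random and 1:1, and both arms receive their setting's usual care. Generalizability and Limitations declares the effect of the whole initiative to be the aim, and a main effect of setting would still yield one pooled effect.

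The reply does not reach the weekly-cigarettes model. The article states its covariate list outright, so the omission is not a detail left to an unseen analysis plan, and the moderator models cover only the primary outcomes.

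**Conclusion.** The point holds as a minor but worthwhile correction. Its sound core is one secondary outcome: weekly cigarettes among continuing smokers is modelled without a baseline value that is already collected, at a cost of roughly 7.5 to 24% in standard error. That range rests on assumed correlations and on dependence acting only through baseline consumption. If the dependence score tracks consumption more closely than assumed, the gain is smaller.

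Leaving out setting costs the primary outcomes little and introduces no bias. Adding it is a cheap guard against chance imbalance in a factor that was not stratified. It is most clearly relevant to the use of other cessation aids, because one setting offers extra support to all smokers. Prognostic value beyond the listed covariates is plausible but not documented.

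**What to change.** In the Models section:

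1. Add log baseline weekly cigarettes to the negative binomial model for follow-up weekly cigarettes. Eligibility requires at least 1 cigarette per week, so the log is defined for every participant.
2. Add recruitment setting as a main effect in the primary and secondary models, and state that the pooled effect across settings remains the target.

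The calculations give little reason to add baseline cigarettes to the other models. The change should be dated and made before outcome results by arm are examined.

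The cost is a wording change, no new data, and one or two extra parameters. That matters only at the earliest interim looks, which begin at 20 completers with seven listed covariates plus allocation already in the model. The standard normal prior that the Sample Size section places on dummy covariates would limit the effect there.

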#### Exploratory Analyses

RCTs traditionally contrast 2 or more groups, however do not address individual variability (also known as heterogenous treatment effects). Some individuals may respond well to an intervention, while others might not, and some may be harmed; however, contrasting 2 heterogenous groups does not identify such differences. Predicting how individuals will respond to an intervention using baseline characteristics is one way of early identification of individuals who may benefit, but also allows us to identify groups of individuals who are less likely to respond well to the intervention [35]. We will therefore learn prediction models from the trial data to predict outcome given baseline values and use a combination of clustering and multinomial regression to identify and label groups of individuals who may be more or less helped by the novel intervention.

We will investigate differences in outcomes between control subjects with respect to the 2 modes of recruitment (online and primary health care). All control subjects will receive links to online resources; however, those who have been recruited at primary health care units will in addition be told about resources available at the unit. Also, participants may react differently to being allocated to the control arm (see Generalizability and Limitations). Thus, these analyses will help to inform potential biases in effect estimates and to inform if offering additional support at the unit is effective above online resources.

### Sample Size

We will use a Bayesian group sequential design to monitor recruitment with interim analyses planned every other week after the first 20 participants have completed the 6-month follow-up. Each of the primary outcomes (prolonged abstinence and point prevalence) will be modelled according to the analysis plan (see Statistical Analysis), and the coefficient for group allocation will be assessed for effect, harm, and futility. Let ß_k,i_ represent the regression coefficient for group allocation at time k for outcome i and D all the data currently accumulated, then the target criteria will be: p(ß_k,i_ > 0 | D) > 97.5% and p(ß_k,i_ > log(1.3) | D) > 50% for effect; p(ß_k,i_ < 0 | D) > 97.5% and p(ß_k,i_ < log(1/1.3) | D) > 50% for harm; and p(log(1/1.3) < ß_k,i_ < log(1.3) | D) > 95% for futility.

For the effect and harm criteria, we will use a standard normal prior for dummy covariates (mean 0, SD 1.0) and a slightly wider prior will be used for the futility criterion (mean 0, SD 2.0). The criteria should be viewed as targets; thus, at each interim analysis, we will evaluate each criterion for each covariate and make a decision if we believe that recruitment should stop or continue. However, recruitment will not exceed 24 months.

Note that this Bayesian approach allows us to look at the data an unlimited number of times without worrying about multiplicities and error rates, as would be necessary using a frequentist approach [36]. Also, since no fixed effect size is prespecified, we reduce the risk of stopping both too early and too late [21].

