The lack of blinding of participants may introduce forms of performance bias, including both movement away and towards behavior change due to disappointment about being in the control group, and while we may hypothesize about the magnitude of this bias, we will consider it a limitation of the trial that we have no means of accounting for quantitatively.

A risk of detection bias stems from the scheme used to decrease attrition bias, by calling participants not responding to initial attempts to collect data (see Data Collection). In such a scenario, it is possible that participants disclose their group allocation to research personnel, who are otherwise blinded, during the follow-up interview. We believe that the advantage of higher follow-up rates gained by calling nonresponders outweighs this risk of bias, and personnel making the calls will be instructed to not prompt and to avoid engaging in conversation about group allocation.

Outcome measures will be self-reported, which may be susceptible to recall and social desirability bias. The Society for Research on Nicotine and Tobacco does however recommend that, in studies with limited face-to-face contact, it is neither required nor desirable to use biochemical verification [25]. Despite this recommendation, results from this trial should be understood under this limitation, as the risk of bias is exacerbated due to participants not being blinded.

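### Research personnel are said to be blinded except for disclosure in calls, but the trial team reviews the between-arm effect every two weeks and decides on stopping while outcomes are still being collected

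*Protocol article*

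**What the plan says.** On blinding, Assignment of Interventions states: "Participants will be aware of their group allocation; however, research personnel will be blinded". After noting that participants complete the questionnaires on their own phones, it adds: "These automated procedures ensure no unblinding". The one exception it allows is the telephone contact with nonresponders, where "it is possible that participants will reveal their allocation to assessors". Generalizability and Limitations repeats this: "it is possible that participants disclose their group allocation to research personnel, who are otherwise blinded, during the follow-up interview".

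On interim analysis, Sample Size has "interim analyses planned every other week after the first 20 participants have completed the 6-month follow-up". For both primary outcomes, "the coefficient for group allocation will be assessed for effect, harm, and futility". The criteria are described as targets, not binding rules, and the decision is left to judgement: "we will evaluate each criterion for each covariate and make a decision if we believe that recruitment should stop or continue". Recruitment is capped at 24 months.

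On outcome collection, Outcomes makes every outcome self-reported. Data Collection provides for nonresponders to be telephoned for the primary outcomes at 3 and 6 months, with at most 5 call attempts.

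**The concern.** A stated property, blinded personnel, meets a stated procedure that removes it for at least some of those personnel. A group coefficient cannot be judged for effect or harm without seeing which way it points and how large it is. The article gives this task, and the discretion that goes with it, to the authors' team as a whole.

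Three things are at stake. First, the trial report would repeat a blinding claim that is not true of everyone it covers. Second, the outcomes are self-reported in an open trial and part of them is collected by telephone. If a caller knew the running result and then heard a participant's arm, the caller would hold an expectation specific to this trial's data. The instruction not to prompt and not to discuss allocation is not aimed at that. Third, stopping is discretionary, so people who have watched the trend decide how long recruitment runs. Generalizability and Limitations discusses performance, detection, recall and social desirability bias, but not knowledge of interim results.

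**Working it through.** No sample size, power or error-rate formula applies. The check compares the sections and counts the looks.

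**1. Scope of the blinding claim.** It covers research personnel without distinguishing roles. The only exception is disclosure by a participant during a call. Interim analysis is not named as an exception.

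**2. What an interim look requires.** Each primary outcome is modelled as in the analysis plan, which under Models means a logistic regression adjusted for baseline characteristics. Fitting it needs outcome, covariates and group for each participant. The effect criterion uses p(β > 0) > 97.5% and p(β > log 1.3) > 50%. The harm criterion uses p(β < 0) > 97.5% and p(β < log(1/1.3)) > 50%. Since log(1/1.3) = −log(1.3), the two differ only in sign. With masked arm labels, effect and harm could not be told apart, so the assessor must know which arm is which.

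**3. Does automation cover it?** The automated procedures described are randomization, notification of allocation and self-completed questionnaires. Interim analysis is not among them. Because the criteria are targets, a person has to read the result and decide.

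**4. Overlap in time with outcome collection.** Looks begin once 20 participants have completed 6 months, and others are then still reaching their 3- and 6-month assessments. Whenever recruitment stops, anyone randomized in the preceding 6 months still has follow-up due, possibly by telephone. Outcome data are therefore collected after the effect has been seen.

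**5. Number of looks during recruitment.**
- Inputs: 24-month cap and one look every two weeks (26 per year), both from Sample Size; first look no earlier than month 6.
- Ceiling: (24 − 6) months × 26/12 per month = 39.
- Calendar count, assuming a start on 1 September 2020 and recruitment to 1 September 2022, and counting the first look:
  - first look 1 March 2021 (month 6): 549 days / 14 = 39 whole intervals, so 40 looks;
  - first look 1 June 2021 (month 9): 457 days / 14 = 32 whole intervals, so 33 looks.
- The 6-to-9-month range for the first look is an assumption, because accrual speed is not given. An early stop would reduce the count.

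**6. Bias.** The article gives neither the share of outcomes collected by telephone nor the frequency of disclosure. No estimate of bias can be derived.

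**The case against.** The strongest reply is that blinding here means blinding to individual allocation. The sentence contrasts participants who know their group with personnel who do not, and the remark about automation follows one about self-completed questionnaires. A pooled coefficient tells a caller nothing about any one participant's arm. This stands as far as callers are concerned. It does not rescue the claim for whoever fits the models on labelled records, since that person has access to allocation itself.

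A reader might infer that the callers, or those managing recruitment, are the people who see the interim results. The article does not say so. The first person plural is ordinary author voice, and the limitations section refers to the personnel making the calls as a group that will be given instructions, which may point to divided roles. What can be said is only that no separation is stated.

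A reader might also take the number of looks as a measure of harm. It is a ceiling on exposure. Calls go only to those who have not answered the link, two reminders and a direct text. A caller who hears the arm could already guess the expected direction from the group's earlier positive trials. Randomization is automatic, so a change in advertising would alter who enrols but not who is allocated where. These points limit the likely bias, and they stand.

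Finally, access rights and firewalls are matters that an article may leave to a fuller document, so their absence alone would be no finding. The point here is narrower: the article affirms blinding in general terms and also affirms a procedure incompatible with it. Even if a fuller document divides the roles, the blinding sentences would still need qualifying.

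**Conclusion.** The point holds in limited form. As written, the statement that research personnel are blinded apart from disclosure in calls cannot be true of those who run or read the fortnightly looks. They know the direction and size of the accumulating effect and, if they work with labelled participant-level data, the allocations. That the data are labelled is inferred from the directional criteria and the adjusted models; the article does not state it.

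The exposure is roughly 33 to 40 looks if recruitment runs the full 24 months and the first look falls between months 6 and 9, and fewer if it stops early. The document does not show that callers are unblinded or that any outcome would be biased, and the size of any bias cannot be derived. The change should be made because it corrects a statement that will carry into the report and closes a route for operational bias at little cost. Sample size, models and thresholds are unaffected.

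**What to change.** 1. In Sample Size, state that the interim models are run, and the stop/continue judgement made, only by named roles that make no follow-up calls and do not manage recruitment.
2. Release only the stop/continue decision to everyone else, and hold back coefficients and arm-level rates until follow-up ends. The separated roles need the full estimates, because the criteria are discretionary targets that cannot be applied from a bare met/not-met flag.
3. Reword Assignment of Interventions and Generalizability and Limitations to say that personnel collecting outcomes are blinded to allocation (subject to disclosure in calls) and to interim results, while those conducting the interim analyses are not.
4. If looks have already taken place, state in the trial report who saw the results and qualify the blinding claim accordingly.

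Cost: access rights, a division of existing roles and a few sentences of text, with no added staff or participants. The downside is that the rest of the team cannot see interim estimates and the discretion over stopping rests with the separated roles.
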